# Effect of acupuncture on patients with insomnia: study protocol for a randomized controlled trial

**DOI:** 10.1186/1745-6215-15-403

**Published:** 2014-10-23

**Keywords:** Insomnia, Acupuncture, Intradermal acupuncture, Clinical trial

## Abstract

**Background:**

Hypnotic drugs tend to be the dominant form of treatment of insomnia, but these come with a number of reported side effects. Acupuncture has been studied as an alternative, resulting in a rising need for methodological research towards verifying its efficacy as insomnia treatment.

**Methods/Design:**

We describe a proposal for a single-center, patient-assessor-blinded, randomized controlled trial with two parallel arms. A total of 38 patients complete screening tests at the first visit, are registered into the clinical trial, and then randomly assigned to the experimental or sham control groups (19 patients for each group). All subjects are clinical insomnia patients who score a 6 or above on the Pittsburgh Sleep Quality Index (PSQI) and meet all inclusion criteria. All subjects are treated with acupuncture and intradermal acupuncture (IDA) three times during the first week. Five sham acupoints are used in the control group. In the experimental group, five real acupoints (PC6, SP6, HT7, KI6, and BL62) are used unilaterally in turn. Sham acupoints are over 1 cm away from each real acupoint.

The primary outcomes are the scores on the Insomnia Severity Index (ISI) and PSQI. Secondary outcomes are the sleep log, the Beck Depression Inventory (BDI), the State-Trait Anxiety Inventory (STAI), the World Health Organization Quality of Life Abbreviated Version (WHOQOL-BREF), the Korean-Auditory Verbal Learning Test (K-AVLT), the Digit Span Test (DS), Event Related Potentials (ERPs) and heart rate variability (HRV) to assess emotional states, sleep quality, cognitive functioning, and electro-physiological changes.

Subjects are assessed at three time points: baseline, post-treatment and follow-up. The duration of the clinical trial is 18 days.

**Discussion:**

To study the enhancement of the effectiveness of acupuncture for insomnia, we test the intradermal acupuncture method, which is performed continuously on the subject’s skin and stimulated at home by the subject every night. In the trial, objective measurements including ERPs and HRV are used to evaluate states of cognition and autonomic nervous system functioning and subjective self-report questionnaires assess insomnia symptoms.

'Sham’ acupuncture points provided by STRICTA are used for the control group.

**Trial registration:**

ClinicalTrials.gov: NCT01956760, registered 5 September 2013.

## Background

Insomnia is commonly defined as a state of being disturbed during daytime activities due to poor sleep quality caused by difficulties in sleep initiation or maintenance despite being in a proper sleep-inducing environment. According to the *International Classification of Sleep Disorders*, *Second Edition* (ISDC-2), insomnia can be categorized as acute insomnia, inadequate sleep hygiene, psychophysiological insomnia (primary insomnia), idiopathic insomnia, paradoxical insomnia, and insomnia associated with a medical condition [1]. Approximately 35% of adults experience insomnia at least once in their lives and almost half suffer seriously. Several studies report that approximately 10% of adults are disrupted in their daily activities due to chronic insomnia [2, 3].

Benzodiazepines, nonbenzodiazepine sedatives, and melatonin agonists are the primary pharmacological treatments for insomnia. Secondary treatment includes antidepressants, diphenhydramine, antipsychotics, and barbiturates [4]. Although effective, these medications often cause side effects such as residual daytime sedation, drowsiness, dizziness, lightheadedness, cognitive impairment, motor incoordination, and dependence [5]. The current most prevalent non-pharmacological therapies for insomnia are sleep hygiene education [6] and cognitive and behavioral psychotherapy, but such treatments require long-term implementation [7].

The effect of acupuncture on insomnia is consistently emerging as an alternative treatment for insomnia. In a systematic review by Yeung *et al*., 20 randomized controlled trials were analyzed to assess the effect of acupuncture on insomnia patients by comparing them with control patients given a benzodiazepine, with results indicating that acupuncture was more effective. The study, however, has certain limitations including an undefined criterion for diagnosis, lack of randomization or blinded conditions, and small sample sizes [8]. Several other studies investigate the effect on acupuncture as a treatment for insomnia by comparing different acupuncture therapies, the effects of using and not using moxa, and comparison with placebo sleeping pills [9–11]. One of these studies shows that auricular acupuncture therapy is more effective for insomnia than two other therapies, and another suggests that acupuncture therapy with moxa is more effective than without [9, 10]. Cheuk *et al*., in a review of 33 clinical trials on the effects of acupuncture on insomnia, conclude that many trials indicate acupuncture treatment improves quality of sleep, but future trials need to be more methodologically rigorous, and that extant trials may be prone to the risk of bias coming from the definition of insomnia, participant characteristics, acupoints, and treatment regimen [12]. Despite the number of studies related to acupuncture and insomnia in the literature however, it is necessary for future trials to provide more methodologically sound evidence of acupuncture’s effect.

It is also is important to include an assessment of psychological/mood states, cognitive functions, and physiological states in future evaluations. According to the diagnostic criteria of insomnia defined by the *Diagnostic and Statistical Manual of Mental Disorders*, *Fourth Edition* (DSM-IV), insomnia is related to anxiety and depression, with many previous neuropsychological studies reporting that lack of sleep may lead to learning-memory disturbances, low attention with a descending level of concentration, and mood changes [13]. Regarding the pathophysiology of insomnia, several studies show that beta electroencephalogram (EEG) activities increase while alpha EEG activities decrease in patients with insomnia [14]. Other studies observed decreasing beta EEG activities in patients with insomnia after cognitive behavior therapy or treatment [15]. Some studies of Event Related Potentials (ERPs) report increasing N1 amplitude and decreasing N350 amplitude in insomnia patients compared to controls; these ERPs’ components are related to hyperarousal and inhibition or regulation of arousal [16, 17]. Additionally, a recent study shows that HF (high frequency) in heart rate variability (HRV) is more dominant than LF (low frequency) in patients with insomnia [18]. However, according to one review, there are no consistent results of HRV in studies of effect in acupuncture treatment, although HRV is a useful tool for observing how acupuncture treatment affects the autonomic nervous system related to sleep cycles [19].

Furthermore, relying on self-report measures - which are subjective and vulnerable to biases - to verify symptom reporting is inadequate. Changes in psychological, physiological, and cognitive functions should be observed using more objective methods, such as neuropsychological tests and electro-physiological measures.

## Methods/Design

### Hypothesis

Insomnia patients treated with acupuncture therapy would have their symptoms more effectively relieved than patients in a sham control group.

### Objectives

To examine significant improvement in the Insomnia Severity Index (ISI), the Pittsburgh Sleep Quality Index (PSQI), and sleep logs of insomnia patients [20, 21];To compare changes in EEG and HRV brought on by acupuncture treatment;To compare changes on the Beck Depression Inventory (BDI), the State-Trait Anxiety Inventory (STAI), the World Health Organization Quality of Life Abbreviated Version (WHOQOL-BREF), the Korean-Auditory Verbal Learning Test (K-AVLT), and the Digit Span Test (DS) from pre- to post-acupuncture treatments [22–26].

### Setting

The study will be performed at the Hwabyung/Stress Clinic in the Kyung Hee University East-West Neo Medical Center at Gangdong, Seoul, as a single-center, patient-assessor-blinded, parallel-group randomized controlled trial. Subjects will be recruited through advertisements on Internet websites, newspapers, and hospital bulletins. Subjects interested in participating in the trial shall be assessed according to inclusion and exclusion criteria by phone. Subjects who meet those criteria will be asked to visit the investigation site.

At the site first visit for screening meeting, subjects will be given more detailed information about the procedures of the study and asked to provide written informed consent if they wish to enroll. Candidate subjects will then complete the PSQI, with a score of 6 or above on the PSQI being used to diagnose subjects as clinical insomnia patients. At this point, inclusion and exclusion criteria will be reassessed, with patients satisfying those criteria being enrolled and registered into the clinical trial.

Registered patients shall be provided with a handout on sleep hygiene education that includes a brief account by the experimenter. They shall also be instructed to complete a sleep log for 2 days prior to their second visit to the center for the baseline evaluation and the first treatment, in order to see whether they had experienced insomnia recently and could properly keep their sleep logs. On the day of the second visit, an expert will check whether patients have completed their sleep logs correctly and re-conduct them on their sleep log writing methods if necessary. The patients will complete their sleep logs during 2 weeks from the second visit.

On the second visit day for the baseline evaluation and the first treatment, all patients will also complete the PSQI, ISI, BDI, STAI, K-AVLT, and the DS, with HRV measured at baseline (prior to first treatment), after the last treatment, and at the 1-week follow-up. EEG recordings will be used as objective measures to validate self-reported insomnia symptoms. ERPs will be measured at baseline and after the last treatment using an odd-ball task. Spontaneous EEGs will also be measured at baseline after the last treatment for spectral analysis. All subjects will complete the WHOQOL-BREF at baseline and at 1-week follow-up. They will also complete the Temperament Character Inventory (TCI) at baseline. All patients will also complete a sleep log every day from baseline to the 1-week follow-up [27]. The Credibility of Treatment Rating Scale (CTRS) will be administered to assess the maintenance of blind conditions after the second treatment [28].

Registered patients shall be randomly divided into the experimental and sham control groups, with an equal number of patients assigned to each group. Patients will then complete either the experimental or sham acupuncture treatment 3 times, with 2- to 3-day intervals, within 1 week.

Figure 1 is an overview of this trial, and Figure 2 is an approximate visit schedule.

**Figure 1 Fig1:**
[figure not shown]
**Study flow chart.**

**Figure 2 Fig2:**
[figure not shown]
**Treatment and assessment schedule.**

### Participants

#### Inclusion criteria

Male or female over 18 under 65 years oldReports clinical symptoms for insomnia and score of 6 or above on the PSQIDemonstrates no problems with communication, both visual and auditory (reading, writing, hearing, speaking, and watching)Signed the written informed consent form for the clinical trial

#### Exclusion criteria

Has taken Western and/or Oriental medicine and/or dietary supplements in the past 2 weeks for insomniaHas a severe neural or psychiatric disorder or a history of major neuropsychiatric disorder (for example, autism, learning disorder, mental retardation, and so on)Has received acupuncture for insomnia treatment in the past monthHas infection or inflammation at the acupointsHas a hemorrhagic disease or anticoagulant intakeHas a serious physical disorderHas participated in any other clinical trial within a month of the screening datePregnancy, breast-feeding, or being a woman of childbearing age not on a proper method of birth control

### Assessments

All assessments in the trial are shown in Figure 2.

### Interventions

In the experimental group, patients will receive needle acupuncture treatment on 5 specified acupoints (PC6, SP6, HT7, KI6, and BL62) for 20 minutes. After 20 minutes, the needles will be removed and intradermal acupuncture (IDA) placed at the same points. The smaller IDA shall be kept attached on the skin for 48 to 72 hours and all patients will be instructed to stimulate themselves before sleep.

In the control group, all interventions shall be the same as those of the experimental group except the location of the acupoints, substituting them with five sham acupoints. The sham acupoints shall be about 1.0 cm from the real acupoints in the experimental group and are spots that do not belong to standard acupoints on the body and are not suitable for actual acupuncture based on anatomical and other conditions. IDA will be placed at five sham acupoints in the control group as well with the same instructions as that of the experimental group.

All acupuncture treatment complies with the Standards for Reporting Interventions in Clinical Trials of Acupuncture (STRICTA) revised in 2010 (see Table 1) [29].

**Table 1 Tab1:** **Interventions details by Standards for Reporting Interventions in Clinical Trials of Acupuncture (STRICTA) items**

Item	Details	Intervention
1. Acupuncture rationale	1a) Style of acupuncture	Traditional needle acupuncture and intradermal acupuncture
	1b) Reasoning for treatment provided based on historical context, literature sources, and/or consensus methods, with references where appropriate	Selected traditional acupuncture points on the 12 meridian system based on the systematic review by Yeung and clinical experiences
	1c) Extent to which treatment was varied	No variation
2. Details of needling	2a) Number of needle insertions per subject per session (mean and range where relevant)	Five needle insertions per 1 session
	2b) Names (or location if no standard name) of points used (uni/bilateral)	*Neiguan* (PC6), *Sanyinjiao* (SP6), *Shenmen* (HT7), *Zhaohai* (KI6), *Shenmai* (BL62), all unilateral.
	2c) Depth of insertion, based on a specified unit of measurement or on a particular tissue level	Depth of needle insertion was at least 5 to10 mm and intradermal acupunctured was 1 to 2 mm
	2d) Response sought	*De-qi* sensation felt by practitioner and subject
	2e) Needle stimulation	No stimulation and just retention without movement Intradermal acupuncture fixed with skin tape and subjects educated to self finger-press on them at nighttime
	2f) Needle retention time	Twenty-minute retention for needles, intradermal acupuncture patched 48 to 72 hours until next session
	2 g) Needle type (diameter, length, and manufacturer or material)	Needles: 0.25 × 40 mm, stainless steel (Dong Bang Medical Co. Ltd, Korea)
		Intradermal acupuncture: 0.18 × 1.3 × 1.5 mm, stainless steel (Dong Bang Medical Co. Ltd, Korea)
3. Treatment regimen	3a) Number of treatment sessions	Three sessions
	3b) Frequency and duration of treatment sessions	Three times per week, interval of 1 to 4 days between sessions
4. Other components of treatment	4a) Details of other interventions administered to the acupuncture group	Sleep hygiene education
	4b) Setting and context of treatment, including instructions to practitioners, and information and explanations to patients	Same practitioner treats every subject at every session in the same outpatient clinic
5. Practitioner background	5) Description of participating acupuncturists (qualification or professional affiliation, years in acupuncture practice, other relevant experience)	Licensed traditional Korean medicine doctor at the Kyung Hee East-West Neo Medical Center at Gangdong with more than 10 years of acupuncture treatment experience
6. Control or comparator interventions	6a) Rationale for the control or comparator in the context of the research question, with sources that justify this choice	Sham acupuncture points
	6b) Precise description of the control or comparison group. If sham acupuncture or any other type of acupuncture-like control is used, provide details as for items 1 to 3 above	Same as intervention group except 2b) and 2d)
		2b) No acupuncture points located away from acupuncture points at least 10 mm
		2d) Without *De-qi* sensation

### Outcomes

#### Primary outcome

The primary outcome of this study will be the changes in the ISI between the baseline, post-treatment assessment, and 1-week follow-up.

The PSQI is an effective self-report questionnaire used to assess the quality of sleep and sleep disturbances. The PSQI is comprised of 19 items consisting of the following components: subjective sleep quality, sleep latency, sleep duration, habitual sleep efficiency, sleep disturbances, use of sleeping medication, and daytime dysfunction. The ISI is a five-point Likert-scale self-rate questionnaire designed to assess the nature, severity, and impact of insomnia, and is widely used to measure responses to treatment in research studies and clinical trials.

#### Secondary outcome

Secondary outcome measures refer to scores on the BDI, STAI, WHOQOL-BREF, K-AVLT, and DS, the weekly average of the components in the sleep logs during the 2-week period, and changes in EEG and HRV between the baseline, post-treatment assessment, and 1-week follow-up (only the EEG was excluded at 1-week follow-up).

The BDI and STAI measure emotional states. The BDI is a self-report scale used in clinics and research commonly for measuring severity of depression through a 21-item multiple-choice questionnaire. The STAI in turn is a 40-question self-report inventory based on a 4-point Likert scale that measures each state and trait of anxiety. Normalized Korean versions of both instruments will be used in the trial. The WHOQOL-BREF will be used for measuring quality of life related to psychological health, social relationships, and environment. It consists of 26 items, a shorter version than the original instrument for research studies and clinical trials. A Korean version of this questionnaire will be used.

The sleep log is a diary to be kept by the patients themselves of their sleeping and waking times as well as additional sleep-related information. It is a useful tool in diagnosing insomnia and monitoring whether treatment is working. Sleep logs include 16 points of information such as sleep-onset latency, waking after sleep onset, time in bed, total sleep time, number of awakenings, sleep quality, and so on.

The K-AVLT is a Korean version of the Auditory Verbal Learning Test normalized for Koreans and is used to evaluate verbal learning and memory abilities in terms of neuropsychological assessment. The DS in turn measures working memory and attention.

EEGs will be recorded from 8 channels (F3, F4, Fz, T3, Cz, T4, Pz and electrooculogram) with QEEG-8 (LXE3208, LAXTHA Inc. Daejeon, Korea). The right earlobe (A1) will be used as a reference electrode during data recording. The electrooculograms (EOG) generated from eye blinks or movements shall be recorded with an electrode placed approximately 1 cm below the subject’s right outer eye can thus. Electro-physiological signals will be amplified (20,000) and filtered (bandpass filter = 0.25 to 50 Hz). EEG signals shall be digitized to 256 Hz.

HRV will be recorded by QECG-3(LXC3203, LAXTHA Inc. Daejeon, Korea) for 5 minutes while the patient maintains a sitting posture.

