### Statistical method

The primary outcome variable for efficacy analysis is ISI, and secondary outcomes are the PSQI, BDI, STAI, WHOQOL-BREF, sleep logs, K-AVLT, DS, EEG, and HRV. Demographics, sleep logs, ISI, PSQI, K-AVLT, Digit Span, STAI, TCI, EEG, and HRV will be analyzed using independent sample *t*-tests at baseline to determine equality of the two groups. A chi-square test will be used to assess sex differences. An efficacy analysis will be done using both per-protocol and intention-to-treat analyses.

Independent *t*-tests between the two groups and a repeated-measures analysis of variance (ANOVA) will be used to determine and compare the effect of acupuncture. The factors are treatment (3 levels: pre-, post-acupuncture and 1-week follow-up) and groups (2 levels: treatment and sham) and their interaction. The significance level was set at *P <*0.05 and *post-hoc* analyses were performed where appropriate.

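### The single three-level time model does not fit three secondary outcomes; for the sleep log, its group-by-time test on the two weekly averages would not measure change from before treatment

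*Protocol article*

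**What the plan says.** Under Statistical method, the efficacy analysis consists of independent t-tests between groups and a repeated-measures ANOVA: "The factors are treatment (3 levels: pre-, post-acupuncture and 1-week follow-up) and groups (2 levels: treatment and sham) and their interaction". No outcome is exempted. The same section lists sleep logs among the variables compared between groups at baseline.

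The measurement schedule is in Setting and Secondary outcome:

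- **WHOQOL-BREF:** "All subjects will complete the WHOQOL-BREF at baseline and at 1-week follow-up".
- **ERPs:** "ERPs will be measured at baseline and after the last treatment using an odd-ball task". Spontaneous EEG is given the same two time points. Secondary outcome acknowledges the gap: "only the EEG was excluded at 1-week follow-up".
- **Sleep log, outcome:** "the weekly average of the components in the sleep logs during the 2-week period". On timing, Setting says: "The patients will complete their sleep logs during 2 weeks from the second visit". Visit 2 is the day of baseline evaluation and first treatment.
- **Sleep log, before treatment:** "They shall also be instructed to complete a sleep log for 2 days prior to their second visit". The stated purpose is to see whether insomnia was recent and whether the patient can keep the log properly. An expert checks the entries at visit 2 and re-instructs the patient if needed.

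The Objectives section puts sleep logs in the first objective, beside the ISI and PSQI.

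**The concern.** A pre/post/follow-up model needs a value at each of the three times. WHOQOL-BREF lacks the middle one, EEG/ERPs lack the last, and the sleep log, as the outcome is defined, lacks the first.

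These gaps differ in weight. An outcome with a baseline and one later value still shows change from baseline. An outcome with two values that both follow the first session does not. If the two weekly sleep-log averages go into the group-by-time ANOVA, the interaction compares a week on treatment with the week after it, and a steady benefit of real acupuncture over sham does not appear in it. Because the article leaves the pre level undefined, analysing the logs with no baseline, with the 2-night log as baseline, or with week 1 treated as baseline all remain open, for a diary of 16 items. That choice should be fixed before data are seen.

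**Working it through.** **1. The plan's own figure.** The sample size rests on the ISI and is not in dispute. Inputs from Sample size: difference 3.8, SD midway between 4.0 and 3.2 = 3.6, two-sided alpha 5%, power 80%, 20% dropout.

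n per group = 2 × [3.6 × (1.960 + 0.842) / 3.8]² = 14.09, rounded up to 15. Then 15 / 0.8 = 18.75, rounded up to 19 per group, 38 in total. This matches the plan.

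**2. Does each outcome support the three-level model?** Group, three-level time and their interaction need 6 fixed-effect parameters. The rank of the design matrix, given the times at which each outcome exists, is:

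| Outcome | Values available | Rank of 6 | Interaction df |
|---|---|---|---|
| ISI | pre, post, follow-up | 6 | 2 |
| WHOQOL-BREF | pre, follow-up | 4 | 1 |
| EEG/ERPs | pre, post | 4 | 1 |
| Sleep log, two weekly averages | week 1, week 2 | 4 | 1 |
| Sleep log, with the 2-day log as pre | 2-day log, week 1, week 2 | 6 | 2 |

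**3. What the two-level version tests.** With two time points, the interaction F equals the squared t from a between-group t-test on the change. A simulated check gave 2.127 for both. For WHOQOL-BREF and EEG/ERPs that change is from baseline, which is the intended quantity.

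For the sleep log, let d0, d1 and d2 be the expected real-minus-sham differences before treatment, in week 1 and in week 2. Randomisation makes d0 = 0. The interaction on the two weekly averages estimates d2 − d1. If d1 = d2 = d, it estimates 0 whatever the size of d. Change from pre-treatment would be d2 − d0 = d.

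**4. Is week 1 a substitute baseline?** No. Setting places three sessions within one week at 2- to 3-day intervals, so session 3 falls 4 to 6 days after visit 2. Week 1 is an on-treatment week.

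**5. How good is the 2-night log as a baseline?** The article gives no night-to-night correlation, so I assume an ICC of 0.2 to 0.5, nights exchangeable within a person, and a stable person-level mean. With single-night variance set to 1:

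- reliability of a k-night mean = k × ICC / [1 + (k − 1) × ICC]
- week-2 mean without covariate: variance V = ICC + (1 − ICC)/7
- change from the 2-night mean: (1 − ICC) × (1/2 + 1/7)
- ANCOVA on the 2-night mean: V − ICC² / [ICC + (1 − ICC)/2]

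| ICC | Reliability, 2 nights | Reliability, 7 nights | No covariate | Change score | ANCOVA |
|---|---|---|---|---|---|
| 0.2 | 0.33 | 0.64 | 0.31 | 0.51 | 0.25 |
| 0.3 | 0.46 | 0.75 | 0.40 | 0.45 | 0.26 |
| 0.5 | 0.67 | 0.88 | 0.57 | 0.32 | 0.24 |

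ANCOVA has the smallest variance throughout. At ICC 0.2 and 0.3, a change score from the 2-night mean is less precise than using no baseline at all. ANCOVA's gain over no covariate is 0.33 × 0.64 = 21% at ICC 0.2 and 0.667 × 0.875 = 58% at ICC 0.5. These are ceilings, since they assume that the person's level does not drift.

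**6. Mixing 2-night and 7-night means in one ANOVA.** Error variances are proportional to 1/2, 1/7 and 1/7. The orthonormal contrasts have variances (1/7 + 1/7)/2 = 0.143 for week 1 against week 2, and (4 × 1/2 + 1/7 + 1/7)/6 = 0.381 for pre against the two weeks. Greenhouse-Geisser epsilon = (0.143 + 0.381)² / [2 × (0.143² + 0.381²)] = 0.83, whatever the ICC.

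**The case against.** The strongest reply is that nothing is lost. Independent t-tests are planned beside the ANOVA, the ANOVA obviously drops to two levels where there are two visits, and the EEG gap is disclosed. For the sleep log, a 2-day pre-treatment log exists and sleep logs are listed for the baseline comparison, which suggests that a baseline was intended; with it the three-level model is estimable. Even without it, a between-group t-test on week 2 is valid under randomisation, and the ANOVA's group main effect would pick up a steady benefit. Time levels by outcome are often left to an analysis plan, and neither that nor Figure 2 is shown.

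Much of this stands, and it rules out three stronger readings that a reader might infer:

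- **That these results cannot be produced.** They can, with methods already named.
- **That the parenthesis about EEG in Secondary outcome is wrong because WHOQOL-BREF also misses a visit.** The parenthesis concerns the follow-up visit only. WHOQOL-BREF is measured then, so the sentence is true and needs no correction.
- **That unequal numbers of nights break an equal-variance assumption.** Both groups have the same 2-night and 7-night means, so homogeneity between groups is untouched. The relevant condition is sphericity, and an epsilon of about 0.83 is a mild departure that a routine correction handles.

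The reply does not settle the sleep log. The article does not merely omit detail: it states one model for all outcomes and defines a sleep-log outcome with no pre-treatment value. Listing sleep logs at baseline hints at the 2-day log without assigning it that role, and its stated purpose is a check.

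**Conclusion.** The point holds in a limited form. The three-level model as stated does not match the schedule for WHOQOL-BREF, EEG/ERPs or the two weekly sleep-log averages (rank 4 of 6 in each case). For the first two the consequence is small, because the two-level version tests the right change. For the sleep log it matters: the interaction on the two weekly averages is not a test of change from pre-treatment, is blind to an effect of equal size in both weeks, and the baseline is left open for a measure in the first objective.

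The algebra in step 3 needs only randomisation. The precision figures depend on the assumed ICC of 0.2 to 0.5 and a stable person mean. Only secondary outcomes are affected; the ISI analysis and N = 38 stay as they are.

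**What to change.** In Statistical method, or in the analysis plan before data are examined:

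1. State that the three-level model applies only to outcomes measured at all three visits.
2. **Sleep log:** make the week-2 mean the main summary, analysed by ANCOVA with the 2-night mean from before visit 2 as covariate. Report week 1 descriptively as on-treatment.
3. **WHOQOL-BREF:** ANCOVA of follow-up on baseline.
4. **EEG/ERPs:** ANCOVA of post-treatment on baseline.
5. Say that the 2-day log is kept as data and is the sleep-log baseline. Give the full diary instruction at visit 1, because the check at visit 2 comes after those entries are made.

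The cost is wording; no visit, measurement or patient is added. The 2-night covariate is noisy, so the gain in power is modest if the night-to-night correlation is low. The trial is already recruiting, so better instruction at visit 1 helps only patients still to be enrolled.
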